# Recurrences of advanced sessile and lateral spreading colorectal adenoma after endoscopic mucosal resection (EMR) thermal ablation versus no adjuvant therapy (RESPECT): a protocol of an international randomized controlled trial

**DOI:** 10.1186/s13063-024-07915-2

**Published:** 2024-02-17

**Keywords:** Colonic polyps, Endoscopic mucosal resection, Local neoplasm recurrence, Thermal ablation, Randomized controlled trial

## Abstract

**Background:**

Nowadays, large benign lateral spreading lesions (LSLs) and sessile polyps in the colorectum are mostly resected by endoscopic mucosal resection (EMR). A major drawback of EMR is the polyp recurrence rate of up to 20%. Snare tip soft coagulation (STSC) is considered an effective technique to reduce recurrence rates. However, clinical trials on STSC have mainly been conducted in expert referral centers. In these studies, polyp recurrence was assessed optically, and additional adjunctive techniques were excluded. In the current trial, we will evaluate the efficacy and safety of STSC in daily practice, by allowing adjunctive techniques during EMR and the use of both optical and histological polyp recurrence to assess recurrences during follow-up.

**Methods:**

The RESPECT study is a multicenter, parallel-group, international single blinded randomized controlled superiority trial performed in the Netherlands and Germany. A total of 306 patients undergoing piecemeal EMR for LSLs or sessile colorectal polyps sized 20–60 mm will be randomized during the procedure after endoscopic complete polyp resection to the intervention or control group. Post-EMR defects allocated to the intervention group will be treated with thermal ablation with STSC of the entire resection margin. Primary outcome will be polyp recurrence by optical and histological confirmation at the first surveillance colonoscopy after 6 months. Secondary outcomes include technical success and complication rates.

**Discussion:**

The RESPECT study will evaluate if STSC is effective in reducing recurrence rates after piecemeal EMR of large colorectal lesions in daily clinical practice performed by expert and non-expert endoscopists. Moreover, endoscopists will be allowed to use adjunctive techniques to remove remaining adenomatous tissue during the procedure. Finally, adenomatous polyp recurrence during follow-up will be defined by histologic identification.

**Trial registration:**

ClinicalTrials.gov NCT05121805. Registered on 16 November 2021. Start recruitment: 17 March 2022. Planned completion of recruitment: 31 April 2025.

## Introduction

### Background and rationale {6a}

Colorectal cancer (CRC) is the third most common cancer worldwide [1]. In most cases, CRC develops from a premalignant polypoid colorectal lesion [2]. Endoscopic detection and subsequent removal of these polyps prevent CRC-related death [3]. The vast majority can be removed endoscopically during routine colonoscopies. Larger (≥ 20 mm) sessile and lateral spreading lesions (LSLs) require more advanced endoscopic resection techniques. Endoscopic mucosal resection (EMR) is considered the standard of care in the West. However, residual or recurrent adenoma after EMR is a recognized limitation with a frequency at first surveillance of up to 20% [4]. Guidelines advise thermal ablation of the resection margins with snare tip soft coagulation (STSC) [5, 6], which has been reported to reduce adenoma recurrence, from 21% in the control group to 5% in the STSC group (*p* < 0.001), with comparable complication rates [7]. This RCT has however some (design) limitations since no adjunctive techniques were allowed during the procedure and all patients were treated in tertiary referral centers by experienced endoscopists. In addition, optical diagnosis was used instead of histological diagnosis during follow-up after EMR (potentially missing 10% of the recurrent polyps [8, 9].

### Objectives {7}

We will conduct a pragmatic multicenter RCT to evaluate the performance of STSC in daily practice in terms of histological polyp recurrence, technical success, and complication rates.

### Trial design {8}

This study is a multicenter patient-blinded randomized controlled superiority trial in which eligible patients will be allocated to the intervention group with STSC or the control group without additional intervention in a 1:1 ratio. The study protocol adheres to the Standard Protocol Items: Recommendations for Interventional Trials (SPIRIT) guideline [10, 11].

## Methods: participants, interventions, and outcomes

### Study setting {9}

The study will be conducted in both academic and non-academic hospitals in Germany and the Netherlands. A list of study sites can be obtained at https://clinicaltrials.gov/ct2/show/NCT05121805.

### Eligibility criteria {10}

Patients aged ≥ 18 years with a colorectal sessile or LSL (Paris classification 0-IIa/b/c, Is) 20–60 mm in size requiring piecemeal EMR (pEMR) are eligible for inclusion. Eligibility is assessed by the performing endoscopist after inspecting the resection site thoroughly. This study allows adjunctive endoscopic techniques, such as cold snare excision, biopsy forceps, and adjunctive ablation in order to achieve a complete resection. Complete resection is defined as the removal of any visible adenomatous tissue. Exclusion criteria are listed in Table 1.

**Table 1 Tab1:** Exclusion criteria

*En bloc* endoscopic mucosal resection
Previously attempted resection
Endoscopic appearance of invasive malignancy (non-lifting Kato D, Kudo V pit pattern)
Histologically confirmed malignancy
Presence or suspicion of inflammatory bowel disease
Macroscopic incomplete resection
Located at the ileo-cecal valve or the appendiceal orifice
Contra-indication for surveillance colonoscopy
American Society of Anesthesiology (ASA) grades IV or V
Pregnancy

### Who will take informed consent? {26a}

Potential eligible patients will be identified prior to EMR by the local investigator. Informed consent will be obtained by the local investigator or coordinating investigator.

### Additional consent provisions for collection and use of participant data and biological specimens {26b}

Not applicable. No additional participant data will be collected. No biological specimens will be collected.

### Interventions

#### Explanation for the choice of comparators {6b}

In order to assess the efficacy of STSC to prevent recurrence, we compare patients receiving STSC with patients not receiving STSC.

#### Intervention description {11a}

Participating endoscopists are instructed to perform STSC by applying 1 to 2 mm of the exposed snare tip directly on the peripheral margins of the EMR site, creating a 2–3-mm rim of ablated tissue around the mucosal defect (Fig. 1). The microprocessor-controlled generator settings will be SOFT COAG mode, 80W, Effect 4 (ERBE Electromedizin, Tübingen, Germany) [7, 12].

**Fig. 1 Fig1:**
[figure not shown]
Pre-EMR image of the polyp (**A**), post-EMR image (**B**), and resection site image after snare tip soft coagulation of the peripheral resection margins (**C**). *EMR* endoscopic mucosal resection

#### Criteria for discontinuing or modifying allocated interventions {11b}

Not applicable. The intervention cannot be modified.

#### Strategies to improve adherence to interventions {11c}

Not applicable. Upon informed consent, the intervention is applied one time during the colonoscopy. Patients can withdraw informed consent at any time during the follow-up period but this will not affect the intervention.

#### Relevant concomitant care permitted or prohibited during the trial {11d}

Not applicable. Concomitant care is not prohibited during the trial.

#### Provisions for post-trial care {30}

Not applicable. Post-trial care is not necessary for this trial.

### Outcomes {12}

In accordance with the Dutch polypectomy guideline, the first surveillance colonoscopy (SC1) is performed 6 months after the resection [13]. The primary outcome is the presence of recurrent adenomatous tissue at the resection site at SC1. Potential recurrence will be assessed by careful optical inspection of the scar, followed by (random) biopsies from each scar quadrant in addition to any areas suspicious for recurrence. The local pathologists will assess the biopsies for microscopic recurrence. Polyp recurrence is defined as histological proof of adenomatous neoplastic tissue in the scar biopsies. Secondary outcomes include technical success and complication rates. Patient and procedural-related characteristics including procedure time, the use of adjunctive resection techniques, and the presence of intra-procedural bleedings are collected.

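### Entry does not require an adenoma but the primary outcome counts only adenomatous tissue, so regrowth of a non-adenomatous index lesion is scored as no recurrence

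*Protocol article*

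**What the plan says.** All references are to the protocol article.

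- **Who enters.** Eligibility criteria {10} takes adults "with a colorectal sessile or LSL (Paris classification 0-IIa/b/c, Is) 20–60 mm in size requiring piecemeal EMR". The abstract describes the same group as those "undergoing piecemeal EMR for LSLs or sessile colorectal polyps sized 20–60 mm". Neither names a histology. The only exclusion in Table 1 that rests on histology is "Histologically confirmed malignancy".
- **What counts as complete resection.** The same section states: "Complete resection is defined as the removal of any visible adenomatous tissue". Macroscopically incomplete resection is an exclusion.
- **What counts as an event.** Outcomes {12} states: "Polyp recurrence is defined as histological proof of adenomatous neoplastic tissue in the scar biopsies". The local pathologists make this reading.
- **The denominator.** Statistical methods {20a} analyses by intention to treat and divides cases by the total number of EMRs in each group. It gives no separate rule for a non-adenomatous index lesion.
- **The title** names the condition as adenoma: "Recurrences of advanced sessile and lateral spreading colorectal adenoma".

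**The concern.** The rule for entry and the rule for an event cover different sets of lesions. A non-adenomatous sessile or lateral spreading lesion of the right size meets every stated entry criterion. If it is incompletely removed and regrows with its own histology, the scar biopsies show residual lesion but no adenomatous tissue, and the patient counts as recurrence-free.

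Three things are at stake.

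- The outcome is called polyp recurrence, but for such lesions it does not measure that. Recurrence is understated in both arms.
- The absolute difference shrinks, because these patients add to the denominators and cannot add to the cases.
- The complete-resection check at entry has the same gap. Taken literally, a visible non-adenomatous remnant does not make a resection incomplete.

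The planned comparison of histological with macroscopic recurrence (Methods for additional analyses {20b}) is also affected. A correctly seen serrated regrowth would appear there as an optical false positive.

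**Working it through.** **1. Compare the passages.** Entry is by morphology, size and technique. Complete resection and recurrence are both by adenomatous tissue. The denominator is all EMRs. Under Implementation {16c}, randomisation follows resection within the same colonoscopy, so the pathology of the resected specimen cannot act as an entry criterion. No other stated rule removes a non-adenomatous lesion from the analysis.

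**2. Reproduce the planned sample size.** Inputs from Sample size {14}: 20% versus 8%, two-sided 5%, 80% power, 15% drop-out, 306 patients (2 × 153). The 1:1 ratio is in Trial design {8}.

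- With pooled variance and no continuity correction, 131 per arm are needed. 131 / 0.85 = 154.1, so 155 per arm and 310 in total, close to 306.
- The stated figure matches 130 / 0.85 = 152.9, so 153 per arm. In reverse, 153 × 0.85 = 130 evaluable per arm.

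Power = Φ{ [ (p1 − p2) − 1.96 √(2p̄(1 − p̄)/n) ] / √( [p1(1 − p1) + p2(1 − p2)]/n ) }, with p̄ = (p1 + p2)/2.

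At n = 130, p1 = 0.20, p2 = 0.08: (0.12 − 1.96 × 0.04304) / 0.04239 = 0.841, so power is 80.0%. The plan's figure is reproduced and has no reserve.

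**3. Illustrate the dilution.** Let s be the share of index lesions that can never be scored as recurrence. The article does not give s; it is assumed here. Assume also that 20% versus 8% holds for adenomatous lesions only. The measured rates are then 20% × (1 − s) and 8% × (1 − s).

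| Assumed s | Measured rates | Absolute difference (points) | Power at 130 per arm |
|---|---|---|---|
| 0% | 20.0% vs 8.0% | 12.0 | 80.0% |
| 5% | 19.0% vs 7.6% | 11.4 | 77.6% |
| 10% | 18.0% vs 7.2% | 10.8 | 74.9% |
| 15% | 17.0% vs 6.8% | 10.2 | 72.1% |
| 20% | 16.0% vs 6.4% | 9.6 | 69.1% |

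The relative risk is 0.40 in every row, because both rates carry the same factor. With no treatment effect both arms are diluted equally, so type I error is not inflated.

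**4. What restricting to adenomatous index lesions would do.** The rates return to 20% versus 8% and the difference to 12 points, but n falls to 130 × (1 − s). At s = 10%, n = 117: (0.12 − 1.96 × 0.04537) / 0.04468 = 0.696, so power is 75.7%. At s = 20%, n = 104 and the same formula gives 70.6%. Restriction therefore corrects what is estimated and recovers little power.

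**The case against.** **The article signals an adenoma trial.** The title, the complete-resection definition and the Discussion all speak of adenoma, and the endpoint fits that intent. This stands as evidence of intent, and it means that restricting the population is as valid a remedy as widening the endpoint. It does not close the gap, because neither a title nor a definition of complete resection is an entry criterion. The Discussion describes the earlier randomised trial as one of adenomatous polyps; this trial's own criteria set no such condition. The full protocol is not shown and may say more, but both the entry list and the outcome definition are stated in full here and do not match.

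**A reader might infer that the trial is underpowered.** The article does not support that. Sample size {14} takes its 20% from a reference that Background and rationale {6a} cites for residual or recurrent adenoma after EMR, in a paragraph on large sessile and lateral spreading lesions. The planning rate may therefore already have an adenoma numerator over mixed lesions, and multiplying by (1 − s) would count the dilution twice. The word serrated does not occur in the article. The share of such lesions, how often they recur, how they respond to STSC and whether local pathologists would call them adenomatous are all unknown. This objection stands in full, and it makes the power figures an illustration only.

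**The sensitivity analysis in {20b} might expose such cases.** It could show visible regrowth without adenomatous histology, but it would not reclassify it, and the primary result would not change.

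**Index histology may be partly known, or may not be collected.** Some lesions may have been biopsied before EMR. Conversely, Plans for assessment and collection of outcomes {18a} does not name index-specimen histology among the collected data. Both points stand, and the second has to be checked before either remedy is adopted.

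**Conclusion.** The mismatch is real and rests on the text alone: entry by morphology, size and technique; recurrence by adenomatous tissue only; denominator of all EMRs. For any non-adenomatous index lesion, regrowth with its own histology is scored as no recurrence, so polyp recurrence and the absolute difference are understated for that part of the population. The relative risk need not change, and type I error is not inflated.

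How much this matters cannot be fixed from the article. The fall in power from 80% to between about 78% and 69% needs three assumptions: a 5% to 20% share, planning rates that apply to adenomas only, and non-adenomatous lesions that are never scored as recurrence. The second is in doubt on the article's own wording. The point is therefore about what the endpoint means and whom it covers. It does not show a shortfall in sample size. It should be corrected because the correction is cheap and the present wording leaves the call to each local pathologist.

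**What to change.** Align population and endpoint in one of two ways, and report the other as a sensitivity analysis.

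1. **Widen the endpoint.** Define recurrence as histologically proven residual or recurrent neoplastic tissue of the index lesion's type, adenomatous or serrated. Change the complete-resection definition in {10} to match; otherwise a visible serrated remnant could pass as complete and later count as recurrence.
2. **Narrow the analysis population.** Keep the adenoma endpoint and restrict its analysis to lesions with adenomatous index histology. Index tissue is removed before randomisation ({16c}) and pathologists are blinded ({17a}), so the restriction does not break the randomised comparison.

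In either case, confirm that index histology is captured in the eCRF, and make the lesion wording consistent across the title, abstract, {10} and {12}.

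Cost: a small protocol amendment after the 52 randomisations reported under Trial status. The first option loses a little comparability with adenoma-only studies. The second analyses slightly fewer patients (for example 117 instead of 130 per arm at an assumed 10% share).

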### Participant timeline {13}

The participant timeline is shown in Table 2.

**Table 2 Tab2:** SPIRIT schedule of enrolment, interventions, and assessments

	Study period			
	Pre-randomization	Primary study period		Follow-up
	− 14 days	pEMR	STSC	+ 180 days
Enrolment				
Eligibility screening	X	X		
Informed consent	X			
Allocation				
Control		X		
Intervention		X	X	
Assessment				
Baseline variables	X			
Procedural variables		X	X	
Primary outcome				X
Secondary outcomes				X

*pEMR* piecemeal endoscopic mucosal resection, *STSC* soft tip snare coagulation

### Sample size {14}

In the colorectum, pEMR has been reported to have a recurrence rate of 20% [4]. Based on the findings of Klein et al. and Kandel et al., we anticipate STSC to be able to reduce the number of recurrences by 60 to 8% [7, 14]. For an 80% power with a 2-sided significance level of 5% and an anticipated drop-out rate of 15%, a total of 306 (2 × 153) patients is required for this study.

### Recruitment {15}

Potential participants will predominately be recruited from national colon screening programs. Identification of eligible patients will be the responsibility of the local principal investigator. Adding additional hospitals to the trial will be considered to ensure sufficient participation enrolment.

### Sequence generation {16a}

Randomization is carried out using a web-based randomization module (Castor EDC, Amsterdam, The Netherlands) and participants are stratified by the center with random block sizes of 2, 4, and 6. Table 2 shows the timing of the enrolment and allocation process.

### Concealment mechanism {16b}

The allocation is revealed once all inclusion and exclusion criteria are met during the colonoscopy. As a result, the allocation sequence is concealed until randomization.

### Implementation {16c}

After endoscopic radical polyp removal, the inclusion and exclusion criteria are re-assessed. When study participation requirements are met, a research assistant not involved in the procedure will randomly assign the patient to the intervention or control group during the colonoscopy. Once the patient is allocated to the intervention group, STSC is performed immediately.

### Who will be blinded {17a}

Patients and pathologists are blinded from the allocated treatment. Due to the study design, endoscopists performing the EMR and the surveillance endoscopy are aware of the allocation. Data analysts will not be blinded.

### Procedure for unblinding if needed {17b}

Not applicable. No need exists for unblinding since only pathologists and patients are blinded.

### Data collection and management

#### Plans for assessment and collection of outcomes {18a}

Data are collected locally on standardized electronic case record forms (eCRF) in Castor EDC by the study coordinators or the local principal investigator. These include patient-related characteristics prior to the pEMR, procedural-related characteristics during the pEMR, and data on the primary and secondary endpoints at the 6-month follow-up time.

### Plans to promote participant retention and complete follow-up {18b}

Participants can leave the study at any time for any reason if they wish to do so. Since the follow-up period is part of standard of care, no additional plans to promote participant retention are made.

### Data management {19}

In order to ensure data quality, all data will be collected and checked by the study coordinator. According to the Dutch Federation of Universities (NFU) standard of risk assessment and monitoring, each participating center will be visited by an independent monitor at pre-defined time points. These monitors will assess the correct handling and storage of study data.

### Confidentiality {27}

Patients will be coded by a numeric randomization code (anonymized) and the principal investigators will be the only ones to have access to this code. The code lists will be stored digitally on the protected hard disc at the local center that included and treated the subject. Its precise location will be written down in the Investigator Site File. The patient data will be recorded in a case record form in CASTOR.

### Plans for collection, laboratory evaluation, and storage of biological specimens for genetic or molecular analysis in this trial/future use {33}

Not applicable. No specimens are collected.

### Statistical methods

#### Statistical methods for primary and secondary outcomes {20a}

The primary outcome will be analyzed according to the intention-to-treat principle with Fisher’s exact test or chi-squared test as appropriate. Recurrences will be reported as recurrence rates (number of cases/total EMRs × 100) for each group. A possible type 1 error will be prevented by including only one lesion per patient. In the unlikely event of a patient having two lesions requiring pEMR and meeting the inclusion/exclusion criteria, only the most distal polyp will be included in the study and the other lesion will be resected during a follow-up colonoscopy. The outcomes of the intention-to-treat analysis will be compared with the per-protocol analysis.

Secondary outcomes include both categorical and continuous variables and will be compared using Student’s *t* test, Wilcoxon rank-sum test, Pearson’s *χ*^2^ test, or Fisher’s exact test as appropriate. For these analyses, a two-tailed *P* < 0.05 will considered to be statistically significant. In case a disbalance exists between potential confounders, multiple regression analysis will be performed for parameters with a *p* ≤ 0.15. Possible risk factors for recurrence will be identified using logistic regression. The Bonferroni correction method will be used to adjust the *p*-value for multiple testing. A cost-effectiveness analysis will be performed in case of superiority of the intervention arm.

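### Safety is a stated aim, but the only criterion given for complications is a difference test at P < 0.05; at low complication rates a non-significant result would say little about safety, and an estimate with a confidence interval would serve better.

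*Protocol article*

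**What the plan says.** The Abstract (Background) of the protocol article announces that "we will evaluate the efficacy and safety of STSC in daily practice". Objectives {7} frames the question "in terms of histological polyp recurrence, technical success, and complication rates", and Outcomes {12} gives complication rates the rank of a secondary outcome: "Secondary outcomes include technical success and complication rates".

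Section {20a} compares secondary outcomes between arms with a t test, Wilcoxon rank-sum test, chi-squared test or Fisher's exact test, and then sets the threshold: "For these analyses, a two-tailed *P* < 0.05 will considered to be statistically significant". Later in the same paragraph, after the sentence on risk factors for recurrence, comes "The Bonferroni correction method will be used to adjust the *p*-value for multiple testing". Neither the number of tests nor the family it covers is given.

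Sample size {14} rests on recurrence only: 20% against 8%, 80% power, two-sided 5%, 15% drop-out, 306 patients. The article gives no expected complication rate, acceptable excess or interval for complications. Adverse event reporting and harms {22} deals with who is told of adverse events, not with how the arms are compared.

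**The concern.** A difference test suits a question in which a significant result is the answer sought. For harm, the reassuring result is the absence of a difference, and a test that fails to reject does not show that. How much a non-significant result is worth depends on the power against a relevant excess, and this trial's size was chosen without regard to complications.

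If Bonferroni is also applied to the complication comparison, the threshold for declaring harm becomes stricter. A correction that guards against false claims of benefit then works against detection of harm.

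The stake is the safety part of the answer. The Discussion presents the trial as a test of STSC in expert and non-expert centres, so complications in ordinary practice belong to the question. A results paper that had only a non-significant p-value to report could not say how large an excess the data leave open.

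**Working it through.** **Inputs.** From Sample size {14}: 153 per arm randomised; 153 × 0.85 = 130 per arm after drop-out. From {20a}: two-sided alpha 0.05, chi-squared or Fisher. The control complication rate is not in the document, so it is assumed and varied. A doubling is used as the reference harm; this too is an assumption.

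**Step 1: the plan's own figure.** With p̄ the mean of the two rates, the normal approximation is

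power = Φ{ [ |p₂ − p₁| − 1.96·√(2p̄(1 − p̄)/n) ] / √[(p₁(1 − p₁) + p₂(1 − p₂))/n] }.

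For 20% against 8% and n = 130: [0.12 − 1.96 × 0.04304] / 0.04239 = 0.841, so power is 80.0%. Then 130/0.85 = 152.9, rounded to 153 per arm and 306 in total. The stated size reproduces, for recurrence.

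**Step 2: power against a doubling of complications.** The same formula for 5% against 10% and n = 153 gives [0.05 − 1.96 × 0.03011] / 0.02998 = −0.301, so power is 38%. Exact enumeration of two independent binomials, 153 per arm, alpha 0.05, gives:

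| Control → STSC | Fisher | Chi-squared |
|---|---|---|
| 3% → 6% | 16% | 24% |
| 5% → 10% | 31% | 38% |
| 6% → 12% | 38% | 45% |
| 7% → 14% | 46% | 52% |
| 8% → 16% | 52% | 58% |
| 10% → 20% | 64% | 70% |

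Power passes 50% just below a 7% control rate for chi-squared and just below 8% for Fisher. Below that point a doubling is missed more often than not; above it, it is detected more often than not. By the normal approximation, 80% power for a doubling is reached from a control rate of about 12.5%.

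**Step 3: variants.**
- Bonferroni for two tests (alpha 0.025), 153 per arm, 5% → 10%: power 21% (Fisher) or 28% (chi-squared). The 50% point moves to about 9% to 10%.
- 130 per arm, alpha 0.05, 5% → 10%: power 25% or 33%. This is relevant if complications are missing for drop-outs, since Table 2 places the secondary outcomes at +180 days.

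**Step 4: what an interval adds.** Newcombe's interval combines the Wilson limits (l, u) of each arm:

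lower = d − √[(p₁ − l₁)² + (u₂ − p₂)²]; upper = d + √[(u₁ − p₁)² + (p₂ − l₂)²].

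Take 17/153 (11.1%; Wilson 7.1% to 17.1%) on STSC and 8/153 (5.2%; Wilson 2.7% to 10.0%) on control.
- The difference is 5.9 points.
- The upper limit is 5.9 + √(5.96² + 2.56²) = 12.4 points.
- The lower limit is 5.9 − √(4.06² + 4.75²) = −0.4 points.
- The tests give p = 0.06 (chi-squared) and p = 0.09 (Fisher), so the result is non-significant while an excess of 12 points remains compatible with the data.

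With 8/153 in each arm the interval is −5.4 to +5.4 points. Even identical observed rates of about 5% would leave a doubling open.

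**The case against.** The strongest reply is that {20a} sets a significance threshold and not a safety rule. A reader might infer that any P of 0.05 or more will be reported as safe or comparable. The document does not say so. The mention of comparable complication rates in Background and rationale {6a} describes an earlier trial and is no rule for this one. That part of the reply stands, and the point is not that the sponsor has committed to a false conclusion.

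Second, low power for a secondary outcome in a superiority trial is not an error, and interval reporting is often left to the full protocol or the analysis plan, neither of which is shown. That also stands as far as missing detail goes. What remains is that the article does state a method for complications, a difference test at P < 0.05, and that method fits a safety aim poorly.

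Third, a reader might infer that a doubling would be missed in most cases. That cannot be said without a condition: the document gives no rate, and the statement fails once the control rate exceeds about 7% to 8%.

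Fourth, the Bonferroni sentence follows directly on the risk-factor regression, and that is its most natural scope. A reader might infer that it will be applied to complications; the wording permits this but does not establish it.

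Finally, an upper confidence limit with no stated acceptable excess is no more a decision rule than the test is. This is correct, and for that reason the fix asks for estimation and not for a new criterion.

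**Conclusion.** The point holds in conditional form. Safety is a named aim, the only stated criterion for complications is a two-tailed difference test, and the sample size was not chosen with complications in mind. With 153 per arm and alpha 0.05, a doubling is missed more often than not if the control complication rate is below about 7% to 8%, or below about 9% to 10% if Bonferroni for two tests applies. At 10% against 20% it is still missed in 30% to 36% of trials, against the 20% miss rate accepted for recurrence.

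These sizes rest on assumed control rates, on a doubling as the harm of interest, and on complete complication data in all randomised patients. The case for an interval does not depend on the rate: it shows at any rate which excesses the data leave open. The point touches neither the primary analysis nor the sample size. It is a cheap improvement.

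**What to change.** In {20a}:

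1. Report complications among all randomised patients as the risk difference, STSC minus control, with a two-sided 95% Newcombe interval as the main safety result. Any p-value is supplementary.
2. Describe the safety evaluation as estimation and give the expected precision: about ±5.4 percentage points if about 5% of each arm (8/153) has a complication.
3. State that a non-significant difference will not be reported as comparable safety.
4. State that the Bonferroni correction does not apply to complications.

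The cost is a few sentences and the intervals in the report, with no added patients, procedures or data. The one downside is that the safety statement may read slightly less favourably than a bare non-significant p-value would.
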